## **PROTOCOL**

### **A. Introduction and Background**

Cognitive training is a promising approach to enhancing brain function, but the generalizability and impact of training outcomes are still controversial, especially in normal, healthy adults (Owen, et al., 2010). Most researchers agree that cognitive training can lead to gains in specific trained skills and abilities (e.g., Ball, et al., 2002). However, studies examining transfer of training benefits to skills and abilities not explicitly trained have yielded mixed results. While some studies have found that cognitive training can produce improvements in untrained tasks (Jaeggi, et al., 2009; Klingberg, 2010; Smith, et al., 2010; Edwards, et al., 2009; COGITO; Kesler, et al., 2011; Finn and MacDonald, 2011), others have failed to demonstrate transfer (Owen, et al., 2010). The specifics of the training, control task, assessments, protocol and sample involved in the study are likely all critical factors in determining which studies result in transfer and which do not. As different researchers have used widely different study designs, it is difficult to pinpoint the key determinants of transfer. In addition, most studies of cognitive training have been underpowered, utilizing small sample sizes that further cloud the interpretation of results.

Large, controlled, repeatable cognitive training study designs are needed to uncover the necessary conditions for successful transfer. Running large, controlled trials of cognitive training exercises in the traditional laboratory-based setting is costly, time consuming and tedious. In person neuropsychological testing requires trained professionals and can take many hours per study participant. Training in a laboratory is even more resource intensive, often involving on-site proctors and typically requiring frequent travel to the study site for participants. When participants are sourced only from the location surrounding the study site (most typically a university or hospital setting), the resulting convenience sample is naturally skewed toward the demographics of the local community, impairing the ability to generalize the findings of the study.

To address these limitations, we propose to conduct a series of very large, online, randomized, controlled trials of cognitive training. The study will use the Lumosity training program for the intervention group and a crossword puzzle sham training active control group. Assessments will be administered immediately before and immediately after a 10-week training period. The assessments include a battery of standard neuropsychological assessments that have been optimized for online administration and a questionnaire probing for changes in everyday cognitive failures.

### **B. Study Design and Procedures**

The study is a two-arm, randomized, active-controlled intervention trial conducted online. No in-person contact will occur between study staff and participants. Participants will be volunteers who choose to click on a link provided in an invitation email sent to a subset of Lumosity users fitting the inclusion and exclusion criteria. From the link, participants will be provided with the consent form, and those who give their informed consent and agree to participate in the study

will then be randomly assigned to either the cognitive training (CT) intervention group or the crossword puzzle active control (AC) group. Those who choose not to participate will maintain their status as Lumosity free users.

Prior to beginning the training, participants will be given a questionnaire probing for changes in everyday cognitive failures, called the Real World Cognition Survey (RWCS), and a battery of standard neuropsychological assessments that have been optimized for online administration, called the Brain Performance Test (BPT). This initial assessment takes approximately 20 minutes to complete. See attached screenshots from the RWCS and BPT.

Following the pre-training assessment, participants will be instructed to begin their training. Participants will be instructed to login to the Lumosity website at least 5 days per week for 10 weeks. Upon logging in, participants will automatically be directed to the appropriate training -- CT or AC. Each daily training session will last approximately 15 minutes, for both CT and AC groups.

At the end of the 10-week training period, all participants will complete the RWCS and BPT. At this point participants who completed all parts of the study will be emailed a free 6-month activation code for Lumosity.com.

### **C. Inclusion/Exclusion Criteria**

Inclusion criteria include being a registered Lumosity user, having access to a networked computer and being able to train at least 15 minutes per day for 5 days a week for 10 weeks. Exclusion criteria include being under 18 years of age.

### **D. Recruitment of Subjects**

Potential volunteers will be invited to participate in the study by clicking on a link provided in an invitation email (see attached) sent to a subset of 35, 000 Lumosity users who meet the inclusion and exclusion criteria for the study. This subset of users will be selected at random. We anticipate that some percentage of users who receive the invitation email will enroll in the study, and a some percentage of those enrolled will complete the full training study. Our goal is to have 10, 000 participants complete the study. For reference, our user-base is currently 40 million subscribed users.

### **E. Consent Process and Timing**

Participants will give their informed consent prior to beginning the training study. They will read the informed consent form online and indicate their consent by clicking a radio button (see attached). Participants will have unlimited time to read through the online form, and will have the opportunity to contact the researchers to ask questions before consenting to participate.

## **F. Risks, Discomforts, and Benefits to Subjects**

There are no known risks as a result of participation in this study. There is the possibility that participants may experience some physical fatigue as result of result of cognitive training, but not any more so than from routine computer use. Participants will be able to take breaks and/or discontinue play as needed. Because participants will have already signed up as free Lumosity users, they will have already provided their contact information for our database. Therefore, there is little to no additional risk of a security breach by participating in the study. As with all of our user data, we will minimize this risk of a security breach by not using the participant's name to identify them on study records. All electronic data will be kept on a secure, encrypted server that is only accessible by Lumosity's research team.

There is a potential benefit of improved cognitive functioning from either or both the cognitive training intervention and the crossword active control intervention. Knowledge from this study will potentially advance research efforts surrounding online cognitive training and ultimately may lead to a better training product.

## **G. Money**

Participants will not receive monetary compensation, nor will they incur any costs.

## **H. Data Analysis and Statistical Analysis**

The data that is stored as part of the study includes demographic variables, assessment performance, and training data. Demographic variables are provided at will by Lumosity users as part of the standard user experience, and include date of birth, gender, and education level. Assessment performance variables include relevant individual raw variables that differ for each assessment, such as number correct, memory span, and presentation time threshold. They also include scaled equivalents of these raw variables based on an earlier reference population. Training data includes information about the timing and performance of each exercise. In the case of Lumosity training, the training variables include an identifier for the game, a timestamp, a game score, a scaled game score, and a variety of game-specific variables that differ depending on the game, such as response times, number of correct responses, and other variables.

All data is stored in a secure MySQL database and/or secured Amazon S3 buckets as part of the Lumosity production website and analytics backend. The Lumosity website has implemented and maintains reasonable security procedures and practices to protect against the unauthorized access, use, modification, destruction or disclosure of users' personal information. For example, we use one or more of SSL encryption, firewalls and self-updating anti-virus software.

The main dependent variables of interest in this study are the amount of improvement on the assessments. The main independent variables of interest are the training condition (crossword puzzles vs. Lumosity intervention) and the amount of training each participant completed. Additional variables including age, gender, level of education and initial performance on the assessments will also likely be included as covariates in order to control for their effects.

The goal of the analysis will be to discern whether the amount of the improvement on the assessments differs depending on the training condition, and whether this difference depends on the amount of training participants' completed. If Lumosity training is more effective than the crossword control condition at improving performance on the assessments, we would also predict that this difference would be dose-dependent. This hypothesis would predict an interaction of training condition and time spent training, wherein increased time spent training on Lumosity should predict larger improvements on the assessment battery than increased time spent training on crossword puzzles.

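### Section H makes the self-chosen amount of training a main independent variable and predicts a condition-by-time interaction as dose-dependence, without saying that this analysis is observational

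*Protocol*

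**What the plan says.** Section B states that consenting users "will then be randomly assigned to either the cognitive training (CT) intervention group or the crossword puzzle active control (AC) group". Dose is not assigned. Both arms get the same instruction: "Participants will be instructed to login to the Lumosity website at least 5 days per week for 10 weeks". Section F leaves the actual amount to the participant: "Participants will be able to take breaks and/or discontinue play as needed".

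Section H defines the outcome: "The main dependent variables of interest in this study are the amount of improvement on the assessments". It then names two explanatory variables of equal rank: "The main independent variables of interest are the training condition (crossword puzzles vs. Lumosity intervention) and the amount of training each participant completed". On adjustment it says: "Additional variables including age, gender, level of education and initial performance on the assessments will also likely be included as covariates".

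The section sets two goals. The first is to learn "whether the amount of the improvement on the assessments differs depending on the training condition", with no reference to dose. The second is whether that difference varies with the amount of training. It adds that, should Lumosity prove better, dose-dependence is also expected: "This hypothesis would predict an interaction of training condition and time spent training, wherein increased time spent training on Lumosity should predict larger improvements". Nothing in the section describes the dose analysis as observational or exploratory, or notes that persistence may be selected differently in the two arms.

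**The concern.** Randomisation makes the arms comparable at baseline. It does not make people who train a lot comparable with people who train a little. Motivation, enjoyment of the assigned activity and perhaps early improvement can all drive the amount of training, and can be related to improvement without any training effect. The dose slope is therefore confounded within each arm.

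If the confounding were equal in both arms it would cancel from the interaction. Here the arms do different activities and all participants are existing Lumosity users, so the reasons for persisting with Lumosity and with crosswords may well differ. The interaction would then pick up a difference in self-selection. None of the listed covariates measures motivation.

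At stake is a reported dose-dependent benefit of Lumosity that is only selection. With a target of 10,000 completers, even a small artefact would reach significance. A second and conditional risk is that amount of training enters the model from which the condition effect is read. That model would adjust for a consequence of assignment.

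**Working it through.** The protocol gives no figure to reproduce: section H states no alpha, power, effect size or SD, and the 10,000 completers in section D are a goal. The check asks how often the tests reject when training has no effect in either arm.

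**From the protocol:** 10,000 completers (section D); two arms (section B).

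**Assumed:** 1:1 allocation, so 5,000 per arm; two-sided 5%; improvement and dose in SD units; an unmeasured trait (call it motivation) correlating *g* with improvement, and *r*(CT) and *r*(AC) with amount of training.

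**1. Interaction.** The spurious dose slope in an arm is g × r. The spurious interaction is g × [r(CT) − r(AC)]. Its standard error is about √(2/5000) = 0.02. With z the ratio of the two, the rejection rate is Φ(z − 1.96) + Φ(−z − 1.96).

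| g | r(CT) − r(AC) | spurious interaction | z | rejection |
|---|---|---|---|---|
| any | 0 | 0 | 0 | 5% |
| 0.1 | 0.1 | 0.01 | 0.5 | about 8% |
| 0.2 | 0.2 | 0.04 | 2.0 | 51.6% |
| 0.3 | 0.2 | 0.06 | 3.0 | 85.1% |
| 0.3 | 0.3 | 0.09 | 4.5 | about 99% |

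**2. Condition, if amount of training is in the model.** Suppose selection is equal in both arms (r = 0.5, g = 0.2) and one arm trains 0.3 SD more on average. The dose slope is 0.5 × 0.2 = 0.10. Adjusting for dose biases the condition effect by 0.10 × 0.3 = 0.03 SD, against the arm that trains more. Then z = 0.03/0.02 = 1.5 and rejection is about 32%.

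**3. Condition, without amount of training.** Motivation is balanced by randomisation, so the expected bias is 0 and rejection is 5%.

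**4. Simulation check.** Least squares, 10,000 participants, 500 runs per scenario, no training effect, g = 0.2 to 0.3, Monte Carlo error about √(0.05 × 0.95/500) = 1 percentage point:

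- Arms compared as randomised: 4.0% to 6.0% in every scenario, mean bias about 0.
- Interaction, r of 0.4 (CT) against 0.2 (AC): 49% to 87%. With 0.35 against 0.25: 18% to 36%.
- Condition term in the model with centred dose and the interaction: 14% to 29% when mean dose differs by 0.3 SD, and 10% to 16% at 0.2 SD.
- Equal selection and equal mean dose: both dose-model tests at 3.6% to 5.4%.

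**5. Scale.** At 5,000 per arm the standardised difference detectable with 80% power is (1.96 + 0.84) × 0.02 = 0.056, so artefacts of the size in step 1 fall where the trial has real power. With half the target (2,500 per arm) the standard error is √(2/2500) = 0.028; the 0.04 artefact then gives z = 1.41 and rejection of about 29%.

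**The case against.** The strongest reply is that section H words its first goal by condition alone, which is a randomised comparison. The section lists variables of interest and does not write a regression equation. Whether the arm effect is fitted with or without dose is commonly left to the SAP, which was not available here. This stands. A reader might infer that both tests lose the protection of randomisation, but the protocol does not support that. Two main independent variables, covariates to be added to them and an interaction point towards one joint model without fixing it. Nor does the protocol say how training time would be coded, so no criticism can rest on the condition coefficient being read at zero minutes.

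A reader might also infer that the interaction is the criterion for efficacy. The text makes it a further prediction that applies if Lumosity is better, and nowhere calls it primary or confirmatory.

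The sizes rest on assumed correlations, and bias is not automatic: with equal selection and equal mean dose both tests hold their level. The listed covariates might absorb part of the confounding, and fewer completers would lower the rejection rates. All of this is fair. It limits how large the problem can be said to be, but randomisation does not guarantee equal selection, and the covariates do not capture motivation directly.

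**Conclusion.** The point holds for the dose analysis. Section H gives a self-determined, post-randomisation variable main status and predicts its interaction with condition without saying that randomisation does not protect that test. Under the stated assumptions the false-positive rate of the interaction runs from about 5% with equal selection to between 8% and 99% when the motivation-dose correlation differs by 0.1 to 0.3 between arms. The mechanism follows from the design; the percentages follow from the assumed correlations, 1:1 allocation and 10,000 completers.

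For the condition comparison the point is conditional. Fitted without amount of training, the comparison is unbiased. Fitted jointly, it could be off by about 0.03 SD, with about 32% rejection, if mean dose differed by 0.3 SD between arms under the correlations in step 2. The protocol leaves open which of these will be done. It does not show that the randomised comparison is already compromised.

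**What to change.** Amend section H, and match the SAP to it, in two places.

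1. State that the main test is the effect of assigned condition on the assessments, in participants as randomised, adjusted only for variables fixed before randomisation (initial score, age, gender, education), with amount of training not in the model.
2. Keep the dose-dependence prediction, since stating a directional hypothesis in advance is good practice. Label the dose and condition-by-time analyses exploratory and observational, and say that they are not causal evidence.

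An instrumental-variable estimate with assignment as the instrument is not a ready substitute. Both arms train, and section F allows that either activity may improve cognition, so one binary assignment cannot separate the two dose effects.

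The cost is a few sentences and no change to conduct or data collection. The downside is that the dose-response result cannot be presented as causal support for efficacy.
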